**3.11 Dissemination of the information**

The results of this study will be reported using ta mixed dissertation format. Manuscripts for consideration in peer-reviewed journals will be drafted alongside during the finalisation of the dissertation. The proposed chapters will be:

Chapter one: Introduction

Chapter two: Literature review

Chapter three: Methodology

Chapter four: Development of *Cucurbita moschata* seeds recipes and nutrition education lesson on the importance of *Cucurbita moschata* using music.

Chapter five: Socio-economic and environmental parameters, nutritional status of children at baseline and six months after the intervention.

Chapter six: Consumption patterns of *Cucurbita moschata* (butternut) seeds, and their contribution to nutrient intake.

Chapter seven: The efficacy of the consumption of *Cucurbita moschata* seeds between the intervention and control groups, according to changes in zinc and iron status from baseline to post intervention (six months).

Chapter eight: Conclusions and recommendations

At least four articles are envisaged, two national and one international conferences presentations. A technical report will be prepared for sharing with the relevant institutions or government authority like the local and district municipalities, National or provincial Department of Social development, Department of Health, Department of Agriculture, Forestry and Fisheries and Department of Basic Education.

**3.12 [name]’s PHD plan of action:**

| **Item No** | **Description of Activity** | **Time Frame** |
| --- | --- | --- |
|  | Application | 2017 |
|  | Registration | February 2018 |
|  | Proposal/protocol development   - Submission of the draft of proposal | February – March 2018 |
|  | Feedback from the supervisor | April 2018 |
|  | Correction and submission | April 2018 |
|  | Feedback from the supervisor | May 2018 |
|  | Correction and finalization of the proposal | May 2018 |
|  | - Meeting with Supervisor and Co-supervisor at Stellenbosch - Presentation of Protocol to Evaluation Committee | June/July 2018 |
|  | Corrections and submission | 1 week |
|  | Approval of Protocol by the Faculty | July 2018 |
|  | Ethics submission and approval   - SU HREC - UNIVEN Research and Ethics committee | Aug – Sep 2018 |
|  | Permission to conduct the study   - Department of Social development at Provincial office. - Vhembe District Department of Social Development and the Local Municipalities - Selected preschools | October - November 2018 |
|  | Registration | January 2019 |
|  | Purchasing of ingredients & consumables | January 2019 |
|  | Phase 1: Recipe development | January 2019 |
|  | Piloting | February 2019 |
|  | Phase 2: Baseline data collection | April 2021 |
|  | Phase 3: Conduct feeding trial | May 2021 |
|  | Phase 4: Post intervention data collection | November 2021 |
|  | Data capturing and cleaning | November 2021 |
|  | Write up and consultation visit (1 week in Jan) | January-March 2022 |
|  | Consult statistician (data analysis) | January 2022 |
|  | Feedback, 1 week writing retreat and consultation | April 2022 |
|  | Corrections and submission | May 2022 |
|  | Submission for Examination | August 2022 |
|  | Oral Examination | Oct/Nov 2022 |
|  | Graduation | December 2022 |

**Appendix: A: Hedonic Scale**

| **Sensory evaluation form** |
| --- |

**Date of data collection…………………….Subject Code:……………………………….**

TITLE OF THE RESEARCH PROJECT:

Efficacy of consumption of *Cucurbita moschata* seeds in management of zinc and iron status in preschool children in Vhembe district, Limpopo province.

**Adopted from Quality partners company Ltd, 2018.**

**APPENDIX B: Baseline survey Date of data collection…………………….Subject Code:……………………………….**

TITLE OF THE RESEARCH PROJECT:

Efficacy of consumption of *Cucurbita moschata* seeds in management of zinc and iron status in preschool children in Vhembe district, Limpopo province.

**DEMOGRAPHIC DATA**

1. Marital status of mother/caregiver

|  | Code | Mark with an X |
| --- | --- | --- |
| Single | 1 |  |
| Married | 2 |  |
| Widowed | 3 |  |
| Divorced | 4 |  |

2.Highest education of mother

|  | Code | Mark with an X |
| --- | --- | --- |
| Never attended school | 1 |  |
| Grade 1 – 4 | 2 |  |
| Grade 5 – 7 | 3 |  |
| Grade 8 – 10 | 4 |  |
| Grade 11 – 12 | 5 |  |
| Tertiary | 6 |  |

3.Is the mother working?

|  | Code | Mark with an X |
| --- | --- | --- |
| Yes | 1 |  |
| No | 2 |  |

4.Who is responsible for household income?

|  | Code | Mark with an X |
| --- | --- | --- |
| Mother | 1 |  |
| Father | 2 |  |
| Grandparents | 3 |  |
| Mother and Father | 4 |  |
| Other, Specify ………………………… | 5 |  |

5.Type of income/employment

|  | Code | Mark with an X |
| --- | --- | --- |
| Health worker | 1 |  |
| Educator | 2 |  |
| Police | 3 |  |
| Retail |  |  |
| Social grant, Specify………… | 4 |  |
| Other, Specify ………………. | 5 |  |

6.Monthly income of the family/household

|  | Code | Mark with an X |
| --- | --- | --- |
| Less than R500 | 1 |  |
| R1000 – R2000 | 2 |  |
| R2000 – R5000 | 3 |  |
| R6000 – R10000 | 4 |  |
| R10000 above | 5 |  |

7. Does the child receive Child Grant

| Yes | No |
| --- | --- |

8. Any other form of grant

| Yes | No |
| --- | --- |

Comment:………………………………………………………………………………………….

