**3.6.2.5. Measurements**

The following measurements will be carried out during the baseline survey: demographic and environmental factors, anthropometrics, dietary intakes and patterns, and biochemical parameter.

1. ***Physical arrangements***

A separate classroom will be requested to be used to ensure privacy for the children and their parents. Two stations will be arranged; (1) measurements of anthropometrics and interviews, and (2) collection of blood samples.

1. ***Demographic and environmental factors***

In this study, demographic factors will be collected, such as age, gender and socioeconomic status. Environmental factors will include the abiotic (temperature, amount of sunlight, and pH of the water) and the biotic (disease, competition, parasitism, and dietary consumption). A validated questionnaire will be used (**see Appendix B**). Since children are under five, mothers will be requested to provide this information.

1. ***Anthropometrics measurements***

Anthropometrics will include weight, height and mid upper arm circumference will be used to assess nutritional status. The weight and height will be taken twice, and average computed to reduce error.

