***Transferrin saturation***

TRFN reagent is used to measure the TRFN concentration by a turbidimetric method.1,2 In the reaction, TRFN combines with specific antibody to form insoluble antigen-antibody complexes. The SYNCHRON® System(s) automatically dilutes sample and dispenses the appropriate sample and reagent volumes into a cuvette. The ratio used is one-part diluted sample to 37.5 parts reagent. The system monitors the change in absorbance at 340 nanometers. This change in absorbance is proportional to the concentration of transferrin in the sample and is used by the System to calculate and express the transferrin concentration based upon a single-point calibration.

1. ***Tools and specific procedures: Record sheet.***

Data will be collected using a record information sheet for demographic data, environmental parameters, recent food intake, dietary intake, anthropometrics, and biochemical parameters. The record sheet will be developed, and pilot tested to check for anything that could impede the instrument's ability to collect data in economical and systematic fashion.

1. ***Validity and Reliability***

The validity of a measurement instrument is the extent to which the instrument measures what it is supposed to measure. Furthermore, reliability is the consistency with which a measuring instrument yields results with repeated measurements, preferably more than 10 repeats. Both validity and reliability, then, reflect the degree to which we may have errors in our measurements (Leedy and Ormrod, 2010). To ensure validity, the measurements for anthropometry will be taken twice and the average will be calculated, and the developed questionnaire and intervention will be piloted and pre-tested before data collection.

To ensure reliability, the developed questionnaire and educational lesson (the song) will be translated into *Tshivenda* and *Xitsonga*, which are the local language spoken in Musina and Collins Chabane municipalities. Experts from the MER Centre for African languages at the University of Venda will carry this exercise. One expert will translate the questionnaire from English to *Tshivenda* and *Xitsonga* and another expert from the same department will translate the *Tshivenda* and *Xitsonga* version of the questionnaire back to English.

1. ***Data analysis***

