**Table 3.5: Proposed data analysis table**

| **Descriptive Statistics** | **Categorical data** | **Numerical data** | |
| --- | --- | --- | --- |
|  |  | **Normally distributed** | **Non-normally distributed** |
| ***Socio demographic information***   - Age - Gender   ***Anthropometric measures***   - Weight, height, MUAC - Categorization according to Z-scores: height for age, weight for age and BMI for age   ***Nutrient intake from 24hr recall***   - Total intake, - Consumption pattern   ***Dietary patterns***  Frequency of inclusion of food item in the FFQ  Morbidity diary  **Biochemical measures**   - Serum zinc - haemoglobin - Serum Ferritin - C-reactive protein - Transferrin saturation - Serum ferritin | Frequencies n (%) | Mean $\pm$ SD | Median and IQR |
| ***Analytical statistics-*** |  |  |  |
| ***Comparison of micronutrient status by subject characteristics*** | Pearson’s Chi-square test/Fishers exact test | ANOVA/T-test | Kruskal-Wallis/Mann-Whitney U tests |
| ***Association between dietary intakes and micronutrient status*** | Regression analyses with dietary intakes and anthropometric indices as dependent variables and all other as independent | | |
| ***Validation of dietary intake and micronutrient status against the intervention*** | Spearman’s correlation coefficient  Comparison of means/means Weighted kappa statistic for agreement testing  Bland Altman plots for bias and agreement testing | | |

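### Appendix B's household-income bands have two gaps and an overlap, and Retail has no code, so some families cannot be classified unambiguously on these two items

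*Protocol*

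**What the plan says.** Section 3.6.2.5 of the Protocol states that "demographic factors will be collected, such as age, gender and socioeconomic status", and refers to Appendix B for the instrument: "A validated questionnaire will be used". Describing demographic and environmental factors is objective 3.6.2.2.1 at baseline and is repeated as objective 3.6.4.2.1 after the trial. Section 3.6.4.4 says that the baseline parameters and procedures will be used again. Section 3.11 plans a results chapter on socio-economic parameters at baseline and six months.

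In Appendix B, under Demographic data:

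- **Item 6, monthly household income**, has five coded rows: "Less than R500 | 1", then R1000 to R2000 (code 2), R2000 to R5000 (code 3), "R6000 – R10000 | 4" and "R10000 above | 5". It has no line for other answers and no space for the amount.
- **Item 5, type of income or employment**, codes health worker 1, educator 2 and police 3. Retail follows with an empty code cell, then "Social grant, Specify………… | 4" and Other (code 5).

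**The concern.** A categorical item needs categories that cover every possible answer and do not overlap. Item 6 does neither, and item 5 has a category that cannot be entered as a code. The form fixes this at data collection. An income that was never written down cannot be restored by any later analysis plan.

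A family with no valid box will be left missing or placed in a neighbouring band at the field worker's discretion. The form gives no rule for this. Because the same form is used at both surveys, one family with an unchanged income could also be placed differently each time and appear to have changed. The lower gap lies among poor households, which the Protocol's background links to deficiency. At stake is the description of the families and any use of income or occupation as a covariate, not the treatment comparison itself.

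**Working it through.** No sample size, power or error-rate figure is involved, so there is no figure of the plan to reproduce. The check assigns every whole-rand income from R0 to R20000 to the printed bands of Appendix B, item 6.

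| Code | Printed band | Whole-rand values covered |
|---|---|---|
| 1 | below R500 | 0 to 499 |
| 2 | R1000 to R2000 | 1000 to 2000 |
| 3 | R2000 to R5000 | 2000 to 5000 |
| 4 | R6000 to R10000 | 6000 to 10000 |
| 5 | R10000 above | from 10000, or from 10001 if read strictly |

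**Values with no band**

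- R500 to R999: 999 − 500 + 1 = 500 values.
- R5001 to R5999: 5999 − 5001 + 1 = 999 values.
- Together: 500 + 999 = 1,499 values.

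**Values with two bands**

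- R2000, in codes 2 and 3, on either reading of the top band.
- R10000, in codes 4 and 5, only if the top band includes R10000.

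Four examples of following the form literally: R800 has no box, R5500 has no box, R2000 has two boxes, and a retail worker has a box without a code.

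**Could the blank Retail code be an extraction fault?** This is unlikely. The codes run 3, blank, 4, 5, so no number was left over for Retail.

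**How many families?** The documents do not allow a count. The 1,499 values are about 15% of the scale from R0 to R10000 (1,499 / 10,000), but that is a share of the rand scale, not of families. Turning it into families needs an income distribution, and the Protocol gives none.

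**The case against.** The strongest reply is that little depends on these two items.

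- Appendix B also records the mother's education and work, who provides the income, grants, housing, water, sanitation, cooking energy and assets. Socioeconomic status can be described without the income band.
- Balance between arms is better judged on the baseline zinc and iron measures, which are recorded.
- Table 3.5 names only age and gender as socio-demographic information. Its plan of "Regression analyses with dietary intakes and anthropometric indices as dependent variables and all other as independent" could bring income in, but does not name it.
- A retail worker can still be marked with an X and coded at data entry. That answer is uncoded, not wrongly coded.
- The overlaps concern only families at exactly R2000 or, on one reading, exactly R10000.
- Section 3.6.2.5 says that "the developed questionnaire and intervention will be piloted and pre-tested before data collection", which may expose the fault.

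All of this stands, and it limits the point to a minor one. It does not remove the point: piloting might find the error, but the printed form is wrong until someone corrects it, and other good items do not repair a faulty one.

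A reader might go further and infer that socioeconomic status is miscoded for many families. The documents do not support that. Under an assumed log-normal income with assumed medians of R1,500 to R4,000 and log-SDs of 0.7 to 0.9, about 12% to 24% of families would fall in the gaps. Every one of those inputs is a guess, so the result is no evidence that the number is large. The documents likewise do not support treating income as the main check on chance imbalance between preschools.

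**Conclusion.** The defect is real and can be read directly from the form. The income bands are neither exhaustive nor mutually exclusive: R500 to R999 and R5001 to R5999 fit nowhere, R2000 fits twice, and R10000 fits twice if the top band includes its limit. Retail has no code. Some families therefore cannot be classified unambiguously on these two items at either survey.

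The share is unknown and could be close to nil. The finding about the form itself needs no assumption beyond whole-rand incomes and, for R10000 alone, the inclusive reading of the top band. The zinc and iron outcomes, the randomisation and the sample size are untouched. This is a small correction to the instrument, worth making because an uncollected answer cannot be recovered later and because the Protocol calls the questionnaire validated.

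**What to change.** Before the form is used:

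1. Replace the item 6 bands with any contiguous, non-overlapping set. One example is: below R500; R500 to R999; R1000 to R1999; R2000 to R4999; R5000 to R9999; R10000 or more. The exact cut points are a matter of choice.
2. Give Retail code 4 in item 5 and renumber Social grant to 5 and Other to 6.
3. Use the same corrected form at baseline and after the trial, and carry the codes into the translated versions and the data-entry sheet.

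The cost is an edit to two small tables, with no added burden for families. The timetable in section 3.12 places baseline collection in April 2021, and the document does not show whether the form has already been used. If it has, report how many families had no band or two bands, and treat those answers as unclassified rather than reassigning them.

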**BIOPHYSICAL ENVIRONMENT**

1. **Type of house**

| **Type (a)**  **(yes 1; no 2)** | | **Number of rooms (b)** |
| --- | --- | --- |
| Hut |  |  |
| Brick and mortar |  |  |
| Shack |  |  |
| Other |  |  |

1. **Source of Water**

|  | **Source (yes 1; no 2)** | |
| --- | --- | --- |
| 10.1 | Tap in house |  |
| 10.2 | Tap outside |  |
| 10.3 | Communal tap |  |
| 10.4 | River |  |
| 10.5 | Tank (rain water harvest) |  |
| 10.6 | Bore hole |  |
| 10.7 | Spring/ well |  |
| 10.8 | Other |  |

1. **Type of Toilet**

| **Code** | **Type** | **Number and Tick appropriate boxes** |
| --- | --- | --- |
| 11.1 | Flush Toilet in house |  |
| *11*.2 | Flush Toilet outside |  |
| *11*.3 | Pit latrine |  |
| *11*.4 | Bush |  |
| *11*.5 | Other |  |

1. **Type of energy used for cooking in the household**

| **Code** | **Type of energy(yes 1; no 2)** | |
| --- | --- | --- |
| *12*.1 | Firewood |  |
| *12*.2 | Coal/ charcoal |  |
| *12*.3 | Electricity |  |
| *12*.4 | Gas |  |
| *12*.5 | Paraffin |  |
| *12*.6 | Gel |  |
| *12*.7 | Cow dung |  |
| *12*.*11* | Solar energy |  |
| *12*.10 | **Other** |  |

**13. Ownership of other assets**

| **Code** | **Type (yes 1; no 2)** | |
| --- | --- | --- |
| *13*.1 | Radio |  |
| *13*.2 | TV |  |
| *13*.3 | DSTV |  |
| *13*.4 | Video/DVD player |  |
| *13*.5 | House telephone |  |
| *13*.6 | Stove |  |
| *13*.7 | Microwave oven |  |
| *13*.*11* | Dining table and chairs |  |
| *13*.9 | Sofas |  |
| *13*.*10* | Play station (PS-VITA, X-box) |  |
| *13*.11 | Other, specify |  |

**FOOD SYSTEMS INVENTORY**

1. **Place of food purchase**

| **Code** | **Place (yes 1; no 2)** | |
| --- | --- | --- |
| *14*.1 | Local formal shops |  |
| *14*.2 | Spaza shops |  |
| *14*.3 | Shoprite |  |
| *14*.4 | Pick n Pay |  |
| *14*.5 | Spar |  |
| *14*.6 | Boxer |  |
| *14*.7 | USave |  |
| *14*.*8* | Checkers |  |
| *14*.9 | Choppies |  |
| *14*.10 | Game |  |
| *14*.*11* | Street vendors |  |
| *14*.12 | SaveMor |  |
| *14*.13 | OK grocery |  |
| *14*.14 | Pick up wild foods |  |
| *14*.15 | Other |  |

1. **Household food production (plants)**

| **Code** | **Type (yes 1; no 2)** | |
| --- | --- | --- |
| *15*.1 | Garden |  |
| *15*.2 | Orchard/ Fruit tree |  |
| *15*.3 | Field in the Household |  |
| *15*.4 | Fields away from household |  |
| *15*.5 | Small holder farm |  |
| *15*.6 | Large farm |  |
| *15*.7 | **Other** |  |

1. **Places for food storage**

| **Code** | **Type (yes 1; no 2)** | |
| --- | --- | --- |
| *16*.1 | Refrigerator |  |
| *16*.2 | Deep Freezer |  |
| *16*.3 | Dry room storage |  |
| *16*.4 | Cup board |  |
| *16*.5 | Not specific |  |
| *16*.6 | **Other** |  |

1. **Resources for food preparation**

| Code | Type (yes 1; no 2) | |
| --- | --- | --- |
| *17*.1 | Open fire outside |  |
| *17*.2 | Open fire inside |  |
| *17*.3 | Gas stove |  |
| *17*.4 | Paraffin stove (primus) |  |
| *17*.5 | Electric stove |  |
| *17*.6 | Coal stove |  |
| *17*.7 | Gel stove |  |
| *17*.*11* | Microwave |  |
| *17*.12 | Wonder box |  |
| *17*.13 | Other |  |

| **SECTION B: RECORD SHEET** |
| --- |

1. Name of the preschool……………………………………………
2. Child’s ID…………………………………………….
3. (ii.) Date of Birth……………… day………. Month………………year
4. (iii.) Age………………………….
5. Gender:

| 1 | 2 |
| --- | --- |
| Female | Male |

1. Did the child receive Deworming?

| 1 | 2 |
| --- | --- |
| Yes | No |

1. (a) Body weight……………………………… kg

(b) Body weight…………………………… kg

© Average weight…………………………….. kg

1. (a) Height………………………………. cm

(b) Height………………………………. cm

© Average height……………………………. cm

1. (a) MUAC ………………………………… cm

(b) MUAC………………………………… cm

© Average MUAC …………………. Cm

27 Was the faeces of the collected?

| 1 | 2 |
| --- | --- |
| Yes | No |

28.Temperature of the participants……………………………………

29.Has your child suffered from any health conditions in the last 15 days?

…………………………………………………………………………………………………………………………………………………………………………………………

30.Does the child have a Road to Health Booklet (RtHB)?

| Yes | No |
| --- | --- |

31. Has the child completed all immunisations?

| Yes | No |
| --- | --- |

Comment ………………………………………………………………………………..

32 Blood sample taken:

| Yes | No |
| --- | --- |

- 1. Time of blood collection………………………………
  2. Time of the previous meal……………………………

**3.3 Morbidity checklist**

| **Diseases** | **Mark with X** |
| --- | --- |
| **Diseases of the respiratory system** |  |
| Flu |  |
| Throat problems |  |
| Asthma/bronchitis |  |
| Pneumonia |  |
| **Signs and symptoms, not elsewhere classified** |  |
| Stomachache |  |
| fever |  |
| Headache |  |
| vomiting |  |
| **Infections and parasitic diseases** |  |
| Diarrhea |  |
| Chickenpox |  |
| Worm infections |  |
| Hepatitis |  |
| **Diseases of the ear** |  |
| Earache |  |
| Ear discharge |  |
| Ear problem/inflammation |  |
| **Diseases of the digestive system** |  |
| Toothache |  |
| Gastrointestinal problem/stomach ache and nausea |  |
| Mouth sores or disease |  |
| Hernia |  |
| Appendicitis |  |
| **Diseases of the skin** |  |
| Wound |  |
| Allergy |  |
| Tumor or abscess |  |
| Itching |  |
|  |  |

**APPENDIX C: 24-hour recall**

| **Section: Dietary Patterns and Intakes of children** |
| --- |

**Please describe the foods (meals and snacks) that you ate yesterday during the day and night, whether at home or outside the home. Start with the first food eaten in the morning**

*Write down all food and drinks mentioned by the respondent. When the respondent has finished probe for meals and snacks not mentioned*

| **Meal** | **Time of meal** | **Food item description** |
| --- | --- | --- |
| **Breakfast** |  |  |
| **Snack** |  |  |
| **Lunch** |  |  |
| **Snack** |  |  |
| **Dinner** |  |  |
| **Snack** |  |  |

**[Household level: consider foods eaten by the child, and exclude foods purchased and eaten outside of the home or at the preschool]**

*When the respondent recall is complete, fill in the food groups based on the information recorded above. For any food groups not mentioned, ask the respondent if a food item from this group was consumed.*

| Question  number | Food group | Examples | Yes = 1  No = 0 |
| --- | --- | --- | --- |
|  | CEREALS | corn/maize, rice, wheat, sorghum, millet or any other grains or foods made from these (e.g. bread, noodles, porridge or other grain products) + *insert local foods e.g.* *ugali, nshima, porridge or pastes or other locally* *available grains* |  |
|  | VITAMIN A RICH VEGETABLES AND TUBERS | pumpkin, carrots, squash, or sweet potatoes that are orange inside + *other locally available vitamin-A rich* *vegetables (e.g. red sweet pepper)* |  |
|  | WHITE TUBERS AND ROOTS | white potatoes, white yams, white cassava, or other foods made from roots |  |
|  | DARK GREEN LEAFY VEGETABLES | dark green/leafy vegetables, including wild ones + *locally available vitamin-A rich leaves such as amaranth, cassava leaves, kale, spinach etc.* |  |
|  | OTHER VEGETABLES | other vegetables (e.g. tomato, onion, eggplant),  including wild vegetables |  |
|  | VITAMIN A RICH FRUITS | ripe mangoes, cantaloupe, apricots (fresh or dried), ripe papaya, dried peaches + *other locally available vitamin* *A-rich fruits* |  |
|  | OTHER FRUITS | other fruits, including wild fruits |  |
|  | ORGAN MEAT (IRON RICH) | liver, kidney, heart or other organ meats or blood-based foods |  |
|  | FLESH MEATS | beef, pork, lamb, goat, rabbit, wild game, chicken, duck, or other birds |  |
|  | EGGS | chicken, duck, guinea hen or any other egg |  |
|  | FISH | fresh or dried fish or shellfish |  |
|  | LEGUMES, NUTS AND SEEDS | beans, peas, lentils, nuts, seeds or foods made from  these |  |
|  | MILK AND MILK PRODUCTS | milk, cheese, yogurt or other milk products |  |
|  | OILS AND FATS | oil, fats or butter added to food or used for cooking |  |
|  | RED PALM PRODUCTS | Red palm oil, palm nut or palm nut pulp sauce |  |
|  | SWEETS | sugar, honey, sweetened soda or sugary foods such as chocolates, candies, cookies and cakes |  |
|  | SPICES, CONDIMENTS, BEVERAGES | spices (black pepper, salt), condiments (soy sauce, hot sauce), coffee, tea, alcoholic beverages OR *local*  *examples* |  |
| 47. Total yes: | | | Yes = 1  No = 0 |
| Individual level only | Did you eat anything (meal or snack) OUTSIDE of the home yesterday? | |  |
| Household level only | Did you or anyone in your household eat anything (meal or snack) OUTSIDE of the home yesterday? | |  |

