3.6.2.2.2. To measure the anthropometry of the study participants (Weight, Height, MUAC)

3.6.2.2.3. Determine the dietary diversity scores of participants using 24- hour recall

- - - - 1. Determine dietary patterns of the study participants using FFQ.
        2. To determine serum zinc concentrations among pre-school children using flame atomic absorption spectrophotometer before consuming *Cucurbita moschata* seeds.
        3. To determine the iron status of pre-school children using hemoglobin, serum ferritin, transferrin receptor and C- reactive protein (CRP) before consuming the *Cucurbita moschata* (butternut) seeds.

**3.6.2.3. Design:** The study design will be a cross sectional survey in which the researcher will measure the demographic and environmental factors, anthropometries, diet patterns, zinc and iron status of pre-school children. A cross sectional study is a method that involve observation of a population or a representative subset at one specific point in time (Leedy and Ormrod, 2010). All measurements parameters will be done at one point using a quantitative approach.

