***Figure 4: MUAC measuring tape.***

The MUAC is the circumference of the left upper arm that is measured at the mid-point between the tips of the shoulder and elbow. The participant’s left arm will be bent then the researcher will find and mark the mid-point between the two marks. There arm will be hanging straight down, and a MUAC tape will be wrapped around the arm at the midpoint mark. The MUAC will be measured to the nearest 1m (**see Appendix B**) for recording.

1. ***Dietary intake and patterns***

A one day 24-hour recall will be used to collect detailed information about all foods and beverages consumed using the multiple pass method (Steinfeldt *et al*., 2013). Foods will have been consumed in the past 24 hours, most commonly, from midnight to midnight the previous day (**see Appendix C)**. Six daily intervals will be included, namely: breakfast (period up to 09h00), In-between snack (between 09h00 and 12h00), lunch (12h00 to 14h00), In-between snack (14h00 to 18h00), dinner (18h00 to 20h00), and after dinner (after 20h00). Guardian/parents will provide this information. A FFQ will be used to establish food consumption patterns including the *Cucurbita moschata* seeds. A selected pictorial FFQ will be designed for the children to establish if they know and consume the seeds (**see Appendix D**). Preschool menu will also be evaluated at this stage using the 24 hr recall form for recording at least once a week during the implementation of the intervention.

1. ***Biochemical measurements***

Zinc status will be determined by serum zinc concentrations and iron status via haemoglobin, serum ferritin, transferrin receptor and C- reactive protein (CRP) among pre-school children using flame atomic absorption spectrophotometer. The anthropometric status of the preschool children will be assessed by measuring weight and height to calculate the body mass index (BMI).

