**Appendix F: Food Diary**

**Please describe the foods (meals and snacks) that your child ate yesterday during the day and night at home. Record this once a week during the six months.**

*Month:*

*Day of the week:*

| **Meal** | **Time of meal** | **Food item description** |
| --- | --- | --- |
| **Breakfast** |  |  |
| **Snack** |  |  |
| **Lunch** |  |  |
| **Snack** |  |  |
| **Dinner** |  |  |
| **Snack** |  |  |

**[Each caregiver will be given 35 forms bound to cover 4 days x 6 moths. These will be collected at the end of each month by the field workers]**

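### The 24-hour recall form (Appendix C) is inconsistent about whose intake, and which meals, it records

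*Protocol*

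**What the plan says.** **Respondent.** In Protocol section 3.6.2.5 (dietary intake and patterns), the recall is a one-day, multiple-pass interview, and "Guardian/parents will provide this information".

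**Target.** The objective in section 3.6.2.2 is "Determine the dietary diversity scores of participants using 24- hour recall", and section 3.6.4.2 repeats it after the intervention. The participants are the children. Under section 3.6.4.4 the baseline procedures are used again at six months.

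**Form.** Appendix C is headed "Section: Dietary Patterns and Intakes of children". Its opening prompt reads "Please describe the foods (meals and snacks) that you ate yesterday during the day and night, whether at home or outside the home". After the meal grid comes a bracketed note: "Household level: consider foods eaten by the child, and exclude foods purchased and eaten outside of the home or at the preschool". The interviewer is then told to "fill in the food groups based on the information recorded above". An individual-level closing item asks "Did you eat anything (meal or snack) OUTSIDE of the home yesterday", and a household-level item asks the same of the respondent or anyone in the household.

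**Comparator.** The food diary in Appendix F is also completed by the caregiver. It reads "Please describe the foods (meals and snacks) that your child ate yesterday during the day and night at home".

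**The concern.** A proxy recall has to name the person whose food is being recalled. Here the question put to the parent names the parent. If a parent answers it literally, the meal grid holds the caregiver's day, and the food groups scored from that grid are attributed to the child.

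The form is also unclear about which meals count. The prompt takes in food eaten away from home. The note removes it, and removes preschool food as well. The trial food is served at the preschool, so this choice decides whether the intervention itself enters the diversity score.

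At stake are the dietary results: the diversity score and nutrient intake (data analysis in section 3.6.2.5), the diet and micronutrient-status analysis in Table 3.5, and part of the evidence for the improved eating patterns expected in section 2.5.

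**Working it through.** The point concerns wording and depends on no sample size, rate or effect size. The check sets the lines side by side.

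**1. Whose intake?**

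| Line | Person named |
|---|---|
| Section 3.6.2.5, respondent | parent or guardian |
| Sections 3.6.2.2 and 3.6.4.2, objective | child |
| Appendix C, heading | children |
| Appendix C, opening prompt | respondent |
| Appendix C, bracketed note | child, but labelled household level |
| Appendix C, probe for unmentioned food groups | nobody named |
| Appendix C, individual closing item | respondent |
| Appendix C, household closing item | respondent or anyone in the household |
| Appendix F, food diary prompt | child |

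Within Appendix C the child is named twice (heading and note). The respondent is addressed as an eater three times (prompt and both closing items).

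**2. Does the note repair the prompt?** Not fully. It is printed after the meal grid, so the recall has been taken by the time the interviewer reaches it. The scoring step then works from what was written down: "fill in the food groups based on the information recorded above". An instruction at scoring cannot turn a caregiver's meals into a child's.

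**3. Which meals?** The prompt covers food eaten at home and away from home. The note excludes food eaten outside the home or at the preschool. Both stand on the same form, and no rule says which prevails.

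**4. Does the choice of meals matter between arms?** It can at six months. Under the intervention description in section 3.6.3, the experimental group eats a paste of butternut seeds and flesh at the preschool, and the control group eats mashed flesh there. Appendix C places squash and pumpkin among the vitamin A rich vegetables, and seeds in the group of legumes, nuts and seeds. Suppose the recalled day is a feeding day and the child scores neither group from other food:

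- Preschool food counted: flesh and seeds give 2 groups in the experimental arm and flesh gives 1 in the control arm, so the difference is 2 − 1 = 1 group.
- Preschool food excluded: the trial foods give 0 − 0 = 0.

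This illustrates direction only. The document does not say whether the recalled day will be a feeding day.

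**5. Would planned checks remove the problem?** The validity and reliability text in section 3.6.2.5 provides for translation into two local languages and back-translation. That tests agreement with the English, so a faithful translation keeps the second person. Piloting might expose the fault, but nothing in the protocol tells interviewers to substitute the child for the person addressed.

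**The case against.** The strongest reply is that the form will not be read out blindly. It is led by an interviewer, with instructions to write down and probe. The field staff are nutritionists trained by the researcher, with methods standardised during piloting (section 3.7). The questionnaire is to be pre-tested. The items before the recall, at the end of Appendix B, ask about the child, and the item numbering suggests that the recall continues that questionnaire. Diet is also captured by a food frequency questionnaire and by a food diary that is worded for the child.

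Much of this stands. It makes wholesale reporting of the caregiver's diet unlikely, and it rules out two stronger readings that a reader might infer:

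- **That the form, as printed, simply records the caregiver's diet as the child's.** The document does not support this, because the same form is headed for children and tells the interviewer to consider what the child ate. What it supports is an inconsistency with a risk of misreporting.
- **That the dilution of the diet and status association can be quantified.** This would need the share of caregivers who answer for themselves and the correlation between caregiver and child diets. The document gives neither. Table 3.5 also makes dietary intake the dependent variable in the planned regression, so treating it as a mismeasured exposure does not match the stated analysis.

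The reply does not dispose of the point. Training may correct the wording in practice, but the printed question still names the wrong person, and the conflict over outside and preschool meals remains however well the interviewers know that the child is the subject.

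**Conclusion.** The concern holds as an inconsistency in the instrument: Appendix C does not settle whose intake is recalled or which meals count. Some caregivers may report their own day, and interviewers may apply different scopes. Either would misstate the child's dietary diversity and nutrient intake at baseline and at six months.

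These are secondary dietary measures. The primary aim in section 2.3 concerns zinc and iron status, measured in blood, and this wording does not affect it. No magnitude is claimed. The conclusion assumes only that interviewers use the form substantially as printed. It is worth correcting because the fault is certain, the remedy is nearly free, and answers given for the wrong person cannot be recovered afterwards.

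**What to change.** Before translation and piloting:

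1. Put the child in the opening prompt in place of the respondent, following the proxy wording of Appendix F ("Please describe the foods (meals and snacks) that your child ate yesterday during the day and night at home"), but with the meal scope settled under item 4 instead of the diary's restriction to home.
2. Reword the individual closing item so that it asks whether the child ate outside the home.
3. Delete the household-level closing item and the household label on the bracketed note. Section 3.6.2.5 also uses this form to record the preschool menu, so not every use is at child level, but that use needs no household item either.
4. Reconcile the bracketed exclusion with the prompt. State one scope, say explicitly whether preschool meals (and so the trial food) count towards the score, and use it at both baseline and six months.

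The cost is the rewording of one form. It needs no extra data, staff or participants.
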